## Participants

### Recruitment

Potential participants will be identified and recruited to the trial by general practitioners who work in the healthcare center in Kranj. Patients who seek medical help due to idiopathic CLBP which persists for at least 12 weeks [1] or had at least two acute episodes of LBP in the last 12 months and fulfill the inclusion and exclusion criteria will be referred to a responsible researcher. A researcher will approach the potential participant and inform them of all aspects of the study and provide a written information sheet, which will state that participation is voluntary and that they are free to withdraw at any time without affecting subsequent medical care (Additional file 3). Personal results and treatment summary will be available at the end of the trial to each participant on individual consultation.

There are no expected contraindications during the treatment protocol, except increased LBP, which can arise in some individuals. If so, according to a consultation with the medical doctor and executive researcher, the load and intensity of exercises will be decreased. If the pain exacerbates, the patient will discontinue the program.

### Eligibility

#### Inclusion criteria

Idiopathic CLBP which persists for at least 12 weeks or two acute LBP episodes in the last 12 months.Patients aged 30–60 years.Capable of at least low physical activity to be able to complete the movement therapy program.

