## Background

Chronic low-back pain (CLBP) is one of the most common reasons for seeking medical care and it imposes a significant burden on individuals and society at large. The lifetime prevalence of low-back pain (LBP) is up to 84%. After an initial episode of LBP, 44–78% of people suffer relapses of pain and 26–37% relapses of work absence [1].

Literature suggests several different methods for coping with CLBP [1]. Supervised exercise therapies are among the most commonly advocated treatments for non-specific CLBP [1]. However, findings from a systematic review concluded the most effective model of exercise therapy remains uncertain [1]. Although several supervised randomized controlled trials (RCT) focusing on different approaches for managing the CLBP using movement therapy have been published so far [2–8], there is no evidence about integral movement therapy program for patients with CLBP. Systematic reviews evaluating the effectiveness of supervised exercise therapies commonly conclude that, to date, there is no evidence to support the superiority of one form of exercise over another [9, 10]. RCTs to date include mostly trunk-strengthening exercises (e.g. bird dog, plank) [5, 7, 8, 11, 12].

People with CLBP often report an impaired ability to perform daily activities. LBP can lead to a significant level of disability and physical functioning [13]. It is common for CLBP patients to avoid activity due to the fear of further exacerbating the pain or harming the spine [14]. LBP is correlated with weak core muscles and delayed muscle activation [15]. In accordance with that, we propose an integral movement therapy program, which is focused on simulating the most common daily activities, body positions, and movements, which require coordinated contraction of local and superficial muscles. Developed with expert consensus, this intervention is based on exercise progression (i.e. from stable to unstable body positions, from single-plane to multi-plane movements, and from minimal resistance/load to maximal). The main focus with all exercises and stages is the control of core/spine position.

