## Methods/ design

### Aims and research questions

The primary study aim is to evaluate the efficiency of supervised and individually graded integral movement therapy program in patients with CLBP on pain, quality of life, and functional abilities. Further, the secondary aim is to compare the difference in outcome measures to supervised, conventional local movement therapy. The following research questions are addressed:Does the supervised and individually graded integral movement therapy program have an effect on reducing pain, improving the quality of life and functional abilities in patients with idiopathic CLBP?Does the supervised and individually graded integral movement therapy program have a clinically more significant effect on reducing pain, improving the quality of life and functional abilities compared to the supervised, conventional local movement therapy?Which program has a better effect on specific core stability strength (e.g. maximal isometric trunk flexion, extension and lateral flexion) and proprioception?

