#### Exclusion criteria

Severe spinal stenosis, spondylolisthesis, fibromyalgia.Lumbar spine surgery.Vascular disease.Neurological deficits because of nerve root or spinal cord compression.Ongoing treatment for LBP.Pregnancy.Co-morbid health conditions that could prevent active participation in exercise.

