## Outcome measures

### Primary outcome measures

There are two aspects of primary outcome measures. The first part of the measures is based on different questionnaires: level of disability (ODI questionnaire); physical activity (IPAQ questionnaire); and pain (NRS questionnaire). All questionnaires will be conducted at baseline, immediately after the intervention, and six months and 12 months after finishing the intervention, as medium- and long-term follow-ups. The second part consists of different functional tests: timed up and go test (TUG); sit to stand test; chair seat and reach test (CSR); 6-min walk test (6MWT); Biering Sorensen test (BS); modified Schober test (mSCH); and Sharpened Romberg balance test (SRB). Those will be collected at baseline and immediately after the intervention.

The ODI questionnaire is one of the instruments for measuring disability caused by LBP. The Slovenian version of the ODI questionnaire is a reliable and valid instrument for assessing outcomes of physical therapy in patients with chronic non-specific LBP [18]. IPAQ was developed as an instrument for cross-national monitoring of physical activity and inactivity and has reasonable measurement properties for monitoring population levels of physical activity among adults in diverse settings aged 18–65 years [19]. Pain intensity is frequently measured on an 11-point pain intensity numerical rating scale, where 0 means no pain and 10 is the worst possible pain. On average, a reduction of 2 points or a reduction of approximately 30% in the NRS is considered a clinically important difference [16, 20].

TUG test, sit to stand test, CSR and 6MWT are part of the Senior Fitness Test battery [21]. Specifically, the tests measure the level of physical abilities (strength, endurance, agility) that are impaired in patients with CLBP.

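### Two acute episodes in 12 months qualify a patient and no current pain is required, so NRS and ODI differences may be diluted and recovery from a flare may be read as programme effect

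*Protocol article*

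**What the plan says.** Under Inclusion criteria, the protocol article lists "Idiopathic CLBP which persists for at least 12 weeks or two acute LBP episodes in the last 12 months". The Recruitment section gives the same alternative: "Patients who seek medical help due to idiopathic CLBP which persists for at least 12 weeks [1] or had at least two acute episodes". The two differ slightly, in that the list says two episodes and Recruitment says at least two.

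The other inclusion criteria are age 30–60 and "Capable of at least low physical activity to be able to complete the movement therapy program". The exclusion that comes closest to current symptoms is "Ongoing treatment for LBP". Nothing in either list sets a minimum NRS or ODI, asks for pain at enrolment, or excludes a patient in an acute episode.

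The aims are framed for chronic low-back pain: "The primary study aim is to evaluate the efficiency of supervised and individually graded integral movement therapy program in patients with CLBP on pain". The comparison with local movement therapy is named as the secondary aim. NRS and ODI are among the primary outcomes. For NRS, "a reduction of 2 points or a reduction of approximately 30% in the NRS is considered a clinically important difference". The analysis section sets the clinically important difference at 30% or more, both within and between groups. The Background describes a relapsing condition, in which after a first episode "44–78% of people suffer relapses of pain".

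**The concern.** The episodic route is satisfied by a history. Read literally, it admits two kinds of patient who sit badly with the outcomes. One is between episodes and has little or no pain on the day of baseline assessment. The other is in an acute episode that may settle whichever programme is given.

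The first kind can show little or no reduction on NRS, and possibly on ODI, so any true difference between the programmes is diluted. The second kind improves for reasons unrelated to treatment. That matters most for the primary aim and the first research question, which ask about the integral programme's own effect on pain, "improving the quality of life and functional abilities in patients with idiopathic CLBP". Both arms receive exercise, so nothing in the trial separates natural recovery from a within-arm change. Finally, a conclusion labelled as chronic low-back pain would describe a group that also includes recurrent acute pain, in proportions the article does not plan to report.

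**Working it through.** **1. Which baseline scores can meet the plan's own criterion.** The NRS runs from 0 to 10, and the largest possible reduction equals the baseline score.

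| Baseline NRS | Largest fall | 2-point fall possible? | 30% fall possible? |
|---|---|---|---|
| 0 | 0 | no | undefined (division by 0) |
| 1 | 1 | no | yes (1 to 0 is 100%) |
| 2 | 2 | yes | yes |

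The criterion offers 2 points *or* about 30%, so only NRS 0 is blocked altogether. NRS 1 fails only if the 2-point version is used. The eligibility lists exclude neither score.

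**2. The plan's sample size.** The Sample size section gives 80% power and 40 per group, tied to an improvement of at least 30%. It gives no SD, baseline mean, responder rate or dropout, so 40 can be neither uniquely reproduced nor refuted. Some assumed inputs come close: a 2-point difference with SD 3.2 gives 41 per arm, and responder rates of 20% against 50% give 39. Others do not: 2 points with SD 2.5 gives 25. The figure is not disputed here and serves only as a starting point.

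**3. The effect that 40 per arm detects.** Take alpha 0.05 (analysis section; two-sided is assumed) and 80% power. The standardised difference is

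d = √(2/40) × (1.960 + 0.842) = 0.2236 × 2.802 = 0.626.

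The t-based value is 0.634. The noncentrality is d × √(40/2) = 2.802.

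**4. Dilution.** Let f be the share with no reducible pain, who therefore contribute no between-arm difference. The document gives no f, so 10–40% is an assumption. The mean difference becomes (1 − f) times the full one. Two assumptions about the SD bracket the result:

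- SD unchanged: power = Φ(2.802 × (1 − f) − 1.960)
- SD shrinks with √(1 − f), because patients with nothing to change add little variance: power = Φ(2.802 × √(1 − f) − 1.960)

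| f | Power, SD unchanged | Power, SD shrinking | n per arm for 80%, SD unchanged: 40/(1 − f)² |
|---|---|---|---|
| 0 | 80% | 80% | 40 |
| 10% | 71% | 76% | 50 |
| 20% | 61% | 71% | 63 |
| 30% | 50% | 65% | 82 |
| 40% | 39% | 58% | 112 |

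Example, f = 20%: 2.802 × 0.8 − 1.960 = 0.281, and Φ(0.281) = 61%. With the shrinking SD, 2.802 × 0.894 − 1.960 = 0.546, and Φ(0.546) = 71%.

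These figures are for a plain two-group comparison of a continuous score such as NRS.

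**5. Flares and the within-arm reading.** No arithmetic applies. In the arm comparison, spontaneous recovery falls on both arms alike on average and cancels. In a before–after change within the integral arm it does not cancel, and there is no untreated arm from which to subtract it.

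**The case against.** The strongest reply is that the episodic route is deliberate. It appears in both Recruitment and Inclusion criteria, and a pragmatic trial may reasonably take chronic and recurrent pain together. Allocation is randomised 1:1, so the comparison between programmes remains valid for whoever is enrolled. That stands.

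General practitioners find the patients, and the Recruitment sentence opens with people seeking medical help, which makes pain-free entrants less likely. This also stands in part. Grammatically, however, help-seeking attaches to the 12-week route and only arguably to the episodic one, and the Inclusion criteria list omits it.

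Pain is one of many primary outcomes, and a patient with little current pain may still change on the functional tests. That is correct, and it confines the dilution argument to NRS and ODI. It is also true that natural recovery inflates before–after change in any back-pain patient when there is no untreated arm. The episodic route adds to that problem but does not create it.

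A reader might infer more than the documents support:

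- That some patients certainly start with no pain. The rule permits this; the number is unknown. The 44–78% in the Background is a relapse rate after a first episode, not the share entering by this route.
- That patients at NRS 0 or 1 can never count as improved. A fall from 1 to 0 meets the 30% criterion.
- That the trial cannot answer a question about chronic low-back pain. The 12-week route is open too, and the size of the mixture is not stated.

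**Conclusion.** The point holds as a weakness of the entry rule and should be corrected; it does not invalidate the trial. As written, eligibility lets in patients whose pain cannot fall, and patients whose pain may fall unaided, while the aims speak only of chronic low-back pain. The between-arm comparison is valid for the enrolled mixture but may lose power on NRS and ODI. The within-programme reading required by the primary aim is the more exposed of the two.

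The size cannot be fixed from the document. For an assumed 10–40% with no reducible pain, power falls from a nominal 80% to between 71% and 39% with an unchanged SD, or between 76% and 58% if the SD shrinks with the share. Both ranges rest on an effect back-solved from 40 per arm, a two-sided 5% test and no between-arm effect in the affected share. If few such patients are enrolled, the loss is small.

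**What to change.** 1. For patients still to be enrolled, by either route, require current pain on an NRS with a fixed recall period, high enough for the plan's own criterion to be reachable: above 0 if the 30% criterion is used, at least 2 if the 2-point criterion is used. Align the two wordings of the episode count.
2. Record entry route (persistent for at least 12 weeks, or recurrent episodes) for every patient, including those enrolled since May 2018.
3. Include entry route and baseline score as covariates in the between-arm NRS and ODI analyses.
4. State the target population and the conclusion as chronic or recurrent low-back pain. Give results by entry route as supportive only: out of 80 patients, a subset of unknown size should not carry the conclusion alone.
5. Do not interpret within-arm change as programme effect.
6. Optionally, ask the number of acute episodes at the existing 6- and 12-month contacts, so that benefit in recurrent patients can be seen.

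The cost is slightly slower recruitment, an entry rule that changes partway through, one extra baseline field, and one question at two contacts if item 6 is adopted. The covariates and the population wording cost only text. A pain floor does not remove patients in a flare, and selecting on a higher score does not remove regression to the mean and may add to it. Items 3 and 5 are therefore needed alongside item 1.

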#### Exclusion criteria

Severe spinal stenosis, spondylolisthesis, fibromyalgia.Lumbar spine surgery.Vascular disease.Neurological deficits because of nerve root or spinal cord compression.Ongoing treatment for LBP.Pregnancy.Co-morbid health conditions that could prevent active participation in exercise.

## Interventions

Participants in each group will receive 20 supervised sessions over 10 weeks, twice per week, for approximately 1 h per session. Sessions will be carried out in small groups of up to five participants and will be supervised by an experienced kinesiologist or physiotherapist.

Both therapy programs start with a general warm-up on the elliptic trainer machine for 5 min, followed by a specific warm-up for the next 5 min including hip flexor, hip extensor, and back extensor stretching. Each stretch is repeated once and held for 30 s. Part of the warm-up routine is also learning the squat technique, pelvic-neutral position, and posture corrections. The cool-down routine includes the same stretches as the warm-up, with each stretch repeated twice (Additional file 4, part 1).

Each week, participants will receive a verbal quote of the week – known as back school. Quotes will be focused on posture, core activation and back position during lifting and carrying the loads, self-management of back pain, standing up and sitting down on the floor, pushing and pulling objects, and putting shoes on and taking them off.

Each participant will be asked to keep his/her own exercise diary in order to follow the exercise intensity: body position; color of elastic; number of sets; and repetitions in each set. Participants can move to the next level of exercise when the required number of repetitions and sets are performed without any compensatory movements of the body and with complete core stability.

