### Sample size and sampling procedure

The sample size for this study is estimated based on clinically important improvements in patient measures through an anchor-based approach which was set at ≥ 30% [16]. In this regard, statistical power is considered to be 1-β (80%). Thus, the inclusion of at least 40 patients per group is planned [17]. Participants are allocated in a 1:1 ration to either of the two groups, local or integral, by a sealed envelope randomization system. Once the patient gives consent to enter a trial, an independent person will perform the randomization by picking one envelope out of 80, 40 of each option, and assigning the patient to the group written in the envelope.

Patients are blinded to treatment allocation, although they are informed about receiving exercise therapy without revealing the content of the treatment. Kinesiologists and physiotherapists who perform therapies are not blinded to treatment allocation, but they do not take part in the outcome measurements.

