## Data processing and statistical analyses

All data related to the study will be stored with the highest possible level of security. Questionnaire data, functional tests results, and exercise session diaries are typed into a database for subsequent transfer into SPSS for reporting and statistical analysis. All statistical analysis will be based on an intention-to-treat basis [27]. The investigator performing the analyses is blinded to treatment allocation. Data analysis will be performed using SPSS v19 (IBM Inc., Armonk, NY, USA).

The normality of distribution will be examined for all variables and those found to have a non-normal distribution will be properly transformed before further analyses. For primary and secondary outcome scores, the mean ± SD, median and range will be given for continuous data. Comparison of pre-intervention parameters of the two groups will be determined using two sample unpaired t-test. Differences between groups in the categorical outcome variable (IPAQ) at each time point (baseline, after treatment, and six-month and 12-month follow-ups) will be analyzed using the χ^2^ test and odds ratio. Analysis of variance with repeated measures will be used to identify changes of the functional outcome variables between baseline and after therapy.

For all tests, a *P* value < 0.05 will be considered significant. The minimal clinically important differences within and between groups comparisons are defined as ≥ 30%.

There will be no interim analyses. Only the authors of the protocol and study designers, SP and NŠ, will have access to all data during the intervention.

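### Therapy is delivered in small groups, but the post-treatment and follow-up analyses named in the article treat patients as independent; if groupmates' outcomes are correlated, standard errors will be too small

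*Protocol article*

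**What the plan says.** Under Sample size and sampling procedure, each consenting patient is allocated individually by drawing one of 80 envelopes, and "the inclusion of at least 40 patients per group is planned". That section mentions neither an ICC nor a design effect.

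Under Interventions, treatment in both arms is shared: "Participants in each group will receive 20 supervised sessions over 10 weeks, twice per week". The next sentence adds "Sessions will be carried out in small groups of up to five participants", and says that the sessions "will be supervised by an experienced kinesiologist or physiotherapist". The section does not say whether patients keep the same groupmates throughout.

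Data processing and statistical analyses names three procedures:

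- Pre-intervention parameters are compared between arms, "determined using two sample unpaired t-test".
- The categorical IPAQ result is compared at each time point with a chi-square test and odds ratio.
- The functional outcomes are analysed from baseline to end of therapy with repeated-measures ANOVA.

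The significance rule is a P "value < 0.05 will be considered significant". Nothing in the section refers to session group or supervisor.

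**The concern.** Patients who train together twice a week for ten weeks share a supervisor's feedback, the weekly back-school message and each other's company. Any of these can make groupmates' outcomes more alike than those of two patients from different groups. The two arms follow different exercise programmes, so a session group almost certainly belongs to one arm only. Variation between groups then adds directly to the variance of the arm comparison.

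The chi-square test assumes independent patients. Repeated-measures ANOVA handles the correlation between measurements on one patient, but not the correlation between patients in one group. If that correlation is above zero, intervals for the arm difference will be too narrow, a superiority claim will be made too often, and 40 per arm will carry less information than 40 independent patients.

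An unseen analysis plan does not fully answer this, because the article itself fixes the tests.

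**Working it through.** **Inputs from the article.** 40 patients per arm; power 80%; alpha 0.05, taken as two-sided because sidedness is not stated; group size m of at most 5.

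**Inputs assumed.** ICC of 0.02, 0.05 or 0.10; stable groups of equal size. For the ANOVA, the relevant ICC is that of the change from baseline.

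**The plan's own figure.** The 40 per arm cannot be derived from the article, which gives an improvement of at least 30% but no standard deviation or control-arm rate. Solving backwards, the standardised difference detectable with 40 per arm is

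d = (1.960 + 0.842) × √(2/40) = 0.626.

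This d is used below only as a reference point and is itself an assumption.

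**Formulas.**

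- Design effect: DE = 1 + (m − 1) × ICC
- Ratio of true to naive standard error: √DE
- Effective number per arm: 40/DE
- True type I error of a test that ignores groups: 2 × [1 − Φ(1.96/√DE)]
- Power of an analysis that allows for groups: Φ(d/√(2·DE/40) − 1.96)

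**Example, m = 5 and ICC 0.05.** DE = 1 + 4 × 0.05 = 1.20 and √DE = 1.095. Then 1.96/1.095 = 1.789, which gives a type I error of 7.4%. For power, 0.626/√(2 × 1.20/40) = 2.557, and Φ(2.557 − 1.96) = 72.5%.

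| m | ICC | DE | SE ratio | Effective n per arm | Type I error | Power at d = 0.626 |
|---|---|---|---|---|---|---|
| any | 0 | 1.00 | 1.00 | 40 | 5.0% | 80% |
| 5 | 0.02 | 1.08 | 1.04 | 37.0 | 5.9% | 76.9% |
| 5 | 0.05 | 1.20 | 1.10 | 33.3 | 7.4% | 72.5% |
| 5 | 0.10 | 1.40 | 1.18 | 28.6 | 9.8% | 65.8% |
| 3 | 0.02 | 1.04 | 1.02 | 38.5 | 5.5% | 78.4% |
| 3 | 0.05 | 1.10 | 1.05 | 36.4 | 6.2% | 76.2% |

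**Check by simulation.** In 40,000 simulated trials with eight groups of five per arm, analysed by an ordinary t-test, the type I error was 5.0%, 6.0%, 7.4% and 9.7% at ICC 0, 0.02, 0.05 and 0.10. This agrees with the formula.

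**How well the ICC could be estimated.** Sixteen groups of five leave 16 − 2 = 14 degrees of freedom between groups and 80 − 16 = 64 within. The between-to-within mean-square ratio is distributed as F(14, 64) times (1 + 4·ICC)/(1 − ICC). That multiplier is 1.08/0.98 = 1.10 at ICC 0.02 and 1.20/0.95 = 1.26 at ICC 0.05. The chance that the ratio falls below 1, so that the group variance is estimated at zero, is about 44% and 33%. The power column uses the normal approximation and does not count this loss of degrees of freedom, so it is slightly favourable.

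**The case against.** Much of the case on the other side is sound and sets the limits of the point.

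- **Not every test is affected.** A reader might infer that all three procedures fail. The t-test covers pre-intervention parameters only, and shared sessions cannot correlate values measured before the first session. The same holds for the baseline IPAQ comparison.
- **Pace is not shared.** Load is graded to the individual in both arms, each patient keeps a personal diary, and moving up a level depends on the patient's own performance. This argues for a lower ICC.
- **Five is a maximum and fixed membership is not stated.** Allocation one patient at a time is compatible with open or changing groups, which would dilute the correlation. The m = 5 rows are therefore the upper case.
- **No ICC is given.** A reader might conclude that the 5% error rate is in fact exceeded, or that the trial is in fact underpowered. The article supports neither statement. At ICC 0.02 the effect is small even with full groups.
- **A condensed article may leave recording of session groups and an ICC assumption to a fuller document.** That is fair for those details. It does not cover the choice of tests, which the article states and which does not match the delivery format it describes.

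What stands is the conditional point: the named post-treatment and follow-up analyses cannot show or absorb a group effect if there is one.

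**Conclusion.** The point holds in conditional form. Individual randomisation followed by group delivery in both arms makes correlation between groupmates plausible, and neither the chi-square test nor the repeated-measures ANOVA allows for it.

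Under assumed ICCs of 0.02 to 0.10 and stable groups of five, a nominal 5% test has a true error of about 5.9% to 9.8%. Power at the back-solved difference of about 0.63 falls from 80% to between about 77% and 66%. With groups of three and ICC up to 0.05, the error stays at or below about 6.2%. The effect is thus minor at the low end and material from an ICC of about 0.05 with full groups.

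The article does not show where in this range the trial lies, nor that the correlation is above zero. The case for acting rests on low cost, and on the fact that clustering may be impossible to assess later if group membership goes unrecorded.

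**What to change.** 1. **Record** each patient's session group and supervisor in the database. Recruitment began in May 2018, so do this retrospectively for patients already treated. If membership changes, assign the group attended for most sessions.
2. **Continuous outcomes:** replace the repeated-measures ANOVA with a mixed model that has a random intercept for session group nested in arm, acting on post-treatment values, with Satterthwaite or Kenward-Roger degrees of freedom. The article plans no mixed model, so this changes the model class and is not just one added term.
3. **IPAQ after treatment and at follow-up:** use a logistic equivalent, or cluster-robust inference with a small-sample correction.
4. **Report** the estimated ICC with its interval, noting that it will be imprecise, and show the analysis without the group term as a sensitivity analysis.

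The cost is one or two data fields, some reconstruction of past group membership, slightly wider intervals and fewer degrees of freedom. The group variance may often be estimated at zero. The article plans no interim analyses, so the change can be written down before outcomes are compared between arms.
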